## Abstract

**Background:**

Social activity is a key component in the prevention of cognitive decline. However, face-to-face social intervention has limited accessibility. To address this issue, we developed the “Photo-Integrated Conversation Moderated by Application” (PICMOA), a home-based group conversation intervention using smartphones. This paper introduces the PICMOA intervention and the protocol of the ongoing randomized controlled trial (RCT), which aims to evaluate the effects of PICMOA on the cognitive functioning and psychological well-being of Japanese community dwelling older adults at the risk of cognitive function decline.

**Methods:**

This study uses an RCT design in two parallel group trials with 1:1 allocation. The participants are community dwelling older adults aged 65 years and above, living in an urban city in Japan, with subjective cognitive concerns. In total, 81 participants were allocated to the intervention or control groups. The intervention group receives 30 min of weekly PICMOA sessions at their home for 12 weeks. The PICMOA intervention consists of (1) a photo preparation period before the session and (2) a structured group conversation session talking about the photos that participants took according to a specific theme. The control group receives 30 min of weekly health education videos on a tablet device. The primary outcome is cognitive functioning at pre- and post-phases of the 12-week intervention measured using the Telephone Interview for Cognitive Status in Japanese, semantic and phonemic fluency tests, and the Digit Span Forward and Backward tests. The secondary outcomes are psychological and social aspects including mental status, well-being, loneliness, and social support.

**Discussion:**

Interest is growing in internet-based activities for preventing social isolation. However, the effect of remote conversation interventions on cognitive functioning remains unclear. This study addresses this issue and provides a new avenue of social participation for older adults.

**Clinical trial registration:**

https://www.umin.ac.jp/ctr/, identifier: UMIN000047247.

## 1. Introduction

Cognitive health is a crucial concern for the health and well-being of older adults. Comprehensive interventions for modifiable risk factors could theoretically prevent or delay about 40% of dementias worldwide (Livingston et al., 2020). Social activity is one of the key factors for the prevention of dementia. There is vast empirical evidence on the longitudinal association between low levels of social activity and the occurrence of dementia (e.g., Fratiglioni et al., 2000; Karp et al., 2006; Saczynski et al., 2006; Amieva et al., 2010). A recent meta-analysis suggested that less frequent social contact, low social participation, and loneliness were significantly associated with the incidence of dementia with strengths comparable to other well-known risk factors of dementia (Kuiper et al., 2015). However, no global recommendation was made in the guidelines of the World Health Organization (WHO), as there was insufficient evidence that social activity intervention reduced cognitive decline and the onset of dementia to draw conclusions (World Health Organization, 2019). Therefore, it is hoped that the knowledge about the impact of social activities on cognitive decline will be accumulated through randomized controlled trials (RCTs).

One of the components of social activities is social contact in which people interact through conversations. There is a close association between linguistic ability, which is the underlying function of conversation, and cognitive health. Linguistic deficits often present in patients with mild cognitive impairment (MCI) and early stages of dementia (Taler and Phillips, 2008). Linguistic features may change as cognitive function declines. A previous study identified the characteristics of spontaneous speech among patients with mild to moderate Alzheimer's disease (AD), such as more production of word-finding delay, semantic paraphasia, empty and indefinite phases, and fewer repaired errors (Forbes-McKay et al., 2013). Another study from the Wisconsin Registry for Alzheimer's Prevention reported that features of speech fluency and semantic content in the spoken language declined faster among participants with early MCI than among those who were cognitively stable (Mueller et al., 2018). Some attempts have been made to screen patients with dementia and MCI by linguistic features such as speech volume, tense, and vocabulary (Fraser et al., 2016; Asgari et al., 2017).

In addition to linguistic ability, conversation is a task that stimulates multiple cognitive functions. Conversation requires attention, working memory, inhibition, and cognitive control (Ybarra et al., 2008; Ybarra and Winkielman, 2012) to read the intentions and feelings of others, maintain focus, manage issues flexibly, and control inappropriate behavior. Therefore, we hypothesized the benefits of conversation-based intervention on cognitive function. Based on our hypothesis, we developed our original intervention called Photo-Integrated Conversation Moderated by Robots (PICMOR), which is a structural group conversation program (Otake-Matsuura et al., 2021) and have examined the effect of this conversation-based intervention.

In the PICMOR program, participants have face-to-face conversation sessions in groups of four and talk about the photographs they took according to a pre-decided theme. As a result of utilizing PICMOR in an RCT among healthy older adults, phonemic fluency was significantly improved by following a 30-min weekly session for 12 weeks, compared to the control group in which free group conversations were held in the same frequency (Otake-Matsuura et al., 2021). Moreover, our post-intervention multimodal magnetic resonance imaging (MRI) showed significant differences in brain metrics between the PICMOR and control groups, which could be associated with the beneficial effect of the intervention on phonemic fluency (Sugimoto et al., 2020; Sugimoto and Otake-Matsuura, 2022a,b). For example, compared to the control group, the intervention group had higher resting-state functional connectivity between the left inferior frontal gyrus, one of the most important brain regions for verbal fluency, and right temporal pole which has been associated with semantic processing (Sugimoto et al., 2020). Additionally, resting-state functional connectivity between these regions was positively correlated with the enhanced phonemic fluency score measured by a neuropsychological test. Moreover, we attempted to elucidate neural underpinnings responsible for the intervention-induced enhancement of verbal fluency by analyzing structural characteristics, including brain volume (Sugimoto and Otake-Matsuura, 2022a) and diffusion tensor imaging (DTI) metrics (Sugimoto and Otake-Matsuura, 2022b).

Although the evidence of our intervention has been accumulated, such face-to-face interventions have one limitation: these are not applicable to the population at risk of isolation (e.g., disability, low accessibility area, or pandemic infection) and those who cannot physically access the intervention. In particular, the recent spread of COVID-19 has forced many older adults to become socially isolated. A prior report by Murayama et al. reported that the weighted prevalence (95% confidence interval) of isolation increased from 21.2% (20.7–21.7%) to 27.9% (27.3–28.4%) in Japan during COVID-19 (Murayama et al., 2021). Since social isolation is related to physical, mental, and cognitive health, there is a huge concern about the physical and mental health implications of social isolation and loneliness (Sepúlveda-Loyola et al., 2020).

In these situations, conversations are still possible even at remote locations using remote communication technology that facilitates widespread intervention. Therefore, we developed a smartphone application that provides home-based group conversation intervention through an easy interface, called “Photo-Integrated Conversation Moderated by Application” (PICMOA), based on our previous PICMOR intervention. In a similar study, Dodge et al. conducted an RCT that was a six-week intervention of talking to an interviewer via a PC-based video chat and found its short-term effects on the semantic and phonemic fluency compared to the controls (Dodge et al., 2015). Although there is a growing focus on internet-based social activity intervention to prevent social isolation, the effect of remote conversation intervention on cognitive functioning is still unclear.

Thus, we have conducted this trial to evaluate the effects of PICMOA on cognitive functioning and psychological well-being among older adults at risk of cognitive decline. Considering the aforementioned evidence, we hypothesized that remote conversations through the PICMOA intervention affects the maintenance of cognitive functioning. Additionally, we are interested in studying the effect of social interaction through the intervention on psychological well-being. In this paper, we introduce the overview of the PICMOA intervention and the whole picture of the ongoing RCT protocol utilizing the PICMOA intervention for 12 weeks. This trial uses an RCT design in two parallel group trials with 1:1 allocation and is registered with the University Hospital Medical Information Network (UMIN) clinical trials registry (UMIN000047247).

## 2. Methods

### 2.1. Study setting and eligibility criteria

The participants are community dwelling older adults aged 65 years and above, living in Wako city, which is an urban area in Japan's Saitama Prefecture near the metropolitan area with a population of 83,821 as of March 2020 (Wako city, 2021). Figure 1 shows the flow of the trial for the participants, including the selection process. In addition to age, the other selection criteria include having subjective cognitive concerns; scoring at least 33 in the Telephone Interview for Cognitive Status in Japanese (TICS-J), which indicates no cognitive impairment (Konagaya et al., 2007); available to provide written consent; and available to perform necessary tests on the designated date. The exclusion criteria include neurological impairment, history of previous medications or diseases known to affect the central nervous system, stroke, serious head injury, serious complicating disorder, and under long-term care (defined as those certificated as “care needs levels” or “support need levels” in the public long term care insurance system).

**Figure 1 F1:**
[figure not shown]
Process flow for participants in the study.

Subjective cognitive concerns (part of the inclusion criteria) were screened by three items of cognitive functioning in the Kihon checklist (KCL) (Sewo Sampaio et al., 2016). The KCL is a self-reporting scale widely used to screen the risk population across Japan, designed by a study group from the Ministry of Health, Labor and Welfare in Japan. Municipalities in Japan have used the KCL to assess and screen high-risk individuals who need intervention, and then provide intervention programs based on its result in each domain to prevent future disability and extend healthy life expectancy. The KCL consists of seven dimensions including daily life, physical strength, nutritional status, oral function, the extent of being housebound, cognitive function, and depression risk. The cognitive function domain in the KCL has three items: (1) “Do your family or your friends point out your memory loss?” (2) “Do you make a call by looking up phone numbers?” and (3) “Do you find yourself not knowing today's date?” (Arai and Satake, 2015). Each item has two choices: “Yes” and “No.” At least one risk response to these three items is considered the risk of cognitive decline and defined as cognitive concerns in this study, referring to the prior RCT studies utilizing KCL to screen the participants with subjective cognitive concern (Huang et al., 2020, 2021).

### 2.2. Intervention

The intervention group receives weekly group conversation interventions via smartphone at their home. All participants in the intervention group use PICMOA, which is the smart phone application that provides home-based group conversation for older adults through an easy interface (Figure 2). We prepared the smartphone (Motorola moto g50) with an internet connection and a manual for all participants. The PICMOA application has several functions to facilitate a series of group conversation interventions, including taking photos in daily life, reminiscing about photos taken previously, selecting photos for the intervention session, conversations as intervention sessions, setting an alarm for the intervention, and checking schedules. It was developed based on Jitsi Meet (https://meet.jit.si/) which is an open-source software web conferencing system (Figure 3). The PICMOA intervention was inspired by the PICMOR program, which was a face-to-face group conversation intervention facilitated by a robot used in our previous RCT (Otake-Matsuura et al., 2021). Our series of group conversation interventions consists of (1) a photo preparation period before the session and (2) structured group conversation discussing photos taken by participants according to a specific theme. Figure 4 depicts the flow of the structured group conversation during the PICMOA intervention.

**Figure 2 F2:**
[figure not shown]
Interface of the PICMOA application. **(A)** Home screen, **(B)** screenshot of “Take Photo” option, **(C)** screenshot of “Select Photo” option, **(D)** screenshot during the conversation session, and **(E)** screenshot of “Schedule” option.

**Figure 3 F3:**
[figure not shown]
Brief architecture of the PICMOA application.

**Figure 4 F4:**
[figure not shown]
Flow of the structured group conversation during the PICMOA intervention.

During the one-week preparation period for each intervention session, participants are instructed to take as many photos as possible in their daily life according to the theme of conversation for the next intervention session (e.g., favorite things, neighborhood landmarks) using the camera function in the intervention application. The list of 12 themes of conversation was described in our previous paper (Otake-Matsuura et al., 2021). Then, participants are required to register two photos, which they select from the photos they took during the 1-week preparation period via the application for the intervention session.

The participants join the conversation session in a small group of four people. The conversation system in the application is designed to start automatically on the participants' smartphone at the scheduled time. The group conversation program is structured into presentation and discussion parts. First, one participant presents (presenter) one photo for one minute which is displayed on all participants' smartphones through the application. Subsequently, all other participants ask questions about the photo, and the presenter responds to the questions in a natural conversation context for two minutes. Then, another photo is displayed, and participants continue presenting and discussing the new photo. After one participant presents two photos and all the other participants discuss it, the role of presenter is switched to another participant and the same process is repeated so that participants experience two photos per presenter in one intervention session.

If a participant drops out after allocation to the intervention group, the intensity of the intervention, such as the number of pictures, intervention time, and the number of people to talk to, will change. The bias resulting from inconsistent intervention intensities across groups could directly affect the results and effect sizes. Therefore, in cases where a participant drops out, older volunteers or research staff participate in the intervention session as a substitute to control the intensity of the intervention.

On the other hand, control group participants attend an active control, which is a weekly health education video on the tablet (Lenovo YT-X705L). All participants in the control group are required to watch the health education videos about successful aging for approximately 30 minutes via a webinar (https://zoom.us/) once a week for 12 weeks. Health education videos are provided in a noninteractive way with the participants' cameras and microphones turned off throughout.

### 2.3. Timeline and procedure

#### 2.3.1. Timeline

The recruitment of participants began in April 2022 and ended in September 2022. The intervention is carried out in two phases (the first half and the second half) considering the feasibility (e.g., equipment). As of November 15, 2022, recruitment was completed, and the second phase of intervention is ongoing. The timeline of the procedure was described as a SPIRIT figure in Figure 5.

**Figure 5 F5:**
[figure not shown]
SPIRIT figure – the timeline of the protocol.

#### 2.3.2. Procedure

In the recruitment phase, the municipality government sent recruitment letters to community dwelling older adults, who responded to previous surveys of the municipality and do not have long term care certification, by mailing them in several batches. We also posted flyers on the city's website and placed flyers at city stores. Once our research staffs were contacted by potential participants who expressed their interest in the trial, the eligible participants were required to provide their written informed consent if they agreed to participate after the explanation of the research. The inclusion and exclusion criteria except for the scores of TICS-J were screened at this point.

After obtaining informed consent to participate, questionnaires and standardized neuropsychological batteries were administered as baseline assessments. Based on the scores of TICS-J in the baseline assessment, final screening was done to proceed to the randomization step.

Following the allocation, a letter was sent to each participant to inform them of the group allocation. Next, participants practiced using the equipment (smartphone/ tablet) with the provided manual and timely instruction from research staff, and experienced a test session of PICMOA/health education once. Then, they started the intervention phase for 12 weeks.

#### 2.3.3. Randomization

Stratified randomizations were performed using a permuted block with a 1:1 allocation to one of the two groups: (1) intervention group with PICMOA and (2) control group with health education. Participants were stratified according to sex and sorted based on the TICS-J total scores. Then, permuted block randomization, with a block size of 2, was performed to allocate participants to the group using computer-generated random numbers. The individual in charge of allocation only had access to the following information during the randomization process: ID, TICS-J scores, and sex. All randomization processes were conducted using statistical software R.

### 2.4. Outcomes

#### 2.4.1. Cognitive functioning

The primary endpoint is cognitive functioning at the pre- and post-phase of the 12-week intervention. We hypothesize that PICMOA, i.e., the conversational intervention, may contribute to maintaining or enhancing the linguistic and executive functions among older adults because conversation may be linked to these functions.

To evaluate the intervention effects on cognitive functioning, we have used standardized neuropsychiatry tests. The TICS-J (Konagaya et al., 2007) is used to evaluate global aspects of cognitive functioning. Verbal fluency tests, more specifically, semantic fluency and phonemic fluency tests are introduced to assess retrieval from memory that may also link to executive controlling (Lezak et al., 2012). The verbal fluency test asks to generate the names of animals to test semantic fluency and the words beginning with “ka” to test phonemic fluency. In both tasks, the total number of words produced in one minute is counted. Digit Span Forward and Backward tests from the Wechsler Adult Intelligence Scale – Fourth Edition (WAIS-IV) (Wechsler, 2008) are used for the assessment of simple memory span and working memory capacity, respectively. The Digit Span test requires participants to repeat numbers presented by the examiner in the same order for the Forward test and in reverse order for the Backward test. All neuropsychological test measures are evaluated telephonically by well-trained clinical psychologists. Although this study is an open-label trial, the assessors are blinded for the allocation results to prevent assessment bias.

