### 2.5. Sample size

Based on our prior RCT study using group conversation intervention, we hypothesized the small to medium effect size of the PICMOA intervention on the verbal fluency tests, which measure the cognitive outcomes in this study. We used G^*^power (Faul et al., 2007) for sample size calculation, with 80% power, small to medium effect size (f = 0.175), a two-sided hypothesis test, an analysis of variance model between groups over time, and an alpha level of 5%. The sample size calculation showed that we needed a total of approximately 80 participants considering a 15% drop out. Eighty-one participants were included in the trial and allocated to the intervention or control groups.

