### 2.7. Statistical analyses

To estimate the effect of the PICMOA intervention, the linear mixed models with random intercepts for outcome measurements will be computed. The models will include the following independent variables: groups assignment factor (PICMOA group: 1, control group: 0), time factor (pre: 0, and post: 1), and their interaction term (time × group). The interaction term will be interpreted as the intervention effect. Given that some baseline statuses such as cognitive functioning, psychosocial status, and familiarity with using equipment may influence the effect of this social intervention, we will examine how much the intervention effects vary depending on the levels of these statuses.

All analyses will be performed using R software, and statistical significance threshold will be set as *P* < 0.05.

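### The primary endpoint is a domain of five cognitive tests with no single primary, composite or success rule, and the sample size covers only the two fluency tests at one 5% alpha

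*Protocol article*

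**What the plan says.** Section 2.4.1 defines the endpoint as a domain: "The primary endpoint is cognitive functioning at the pre- and post-phase of the 12-week intervention". The Abstract (Methods) says that it is "measured using the Telephone Interview for Cognitive Status in Japanese, semantic and phonemic fluency tests, and the Digit Span Forward and Backward tests". That makes five scores: TICS-J, semantic fluency, phonemic fluency, Digit Span Forward and Digit Span Backward. Section 2.4.1 describes the same five and ranks none above the others.

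Section 2.7 fits linear mixed models with random intercepts to the outcome measurements. Of the time-by-group term it says: "The interaction term will be interpreted as the intervention effect". For all analyses, the "statistical significance threshold will be set as *P* < 0.05".

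Section 2.5 bases the sample size on a "small to medium effect size of the PICMOA intervention on the verbal fluency tests, which measure the cognitive outcomes in this study". The calculation is made "with 80% power, small to medium effect size (f = 0.175), a two-sided hypothesis test", with an alpha of 5%. It arrives at about 80 participants after allowing for 15% dropout, and 81 were allocated.

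**The concern.** Five tests give five group-by-time interactions and five P-values for one primary question. The article does not say how they combine into an answer. It gives no single primary test, composite, order of testing, or requirement that all or some number of the tests succeed. With P < 0.05 as the only stated threshold, nothing in the article prevents one significant test out of five from being reported as an effect on cognitive functioning. The risk is concrete, because the Introduction summarises the sponsor's prior face-to-face trial by its significant improvement in one measure, phonemic fluency.

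The sample-size section adds a second difficulty. It describes the fluency tests as the measures of the cognitive outcomes, while the Abstract and Section 2.4.1 list five. TICS-J and both Digit Span tests are therefore primary without a stated effect size or power. Even the fluency basis is a pair of tests, yet only one 5% alpha is used.

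At stake are the type I error rate on the primary question and the meaning of the stated 80% power.

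**Working it through.** **Inputs from the article.** Five primary measures (Abstract; Section 2.4.1). P < 0.05 for all analyses (Section 2.7). f = 0.175, 80% power, alpha 5% two-sided, 15% dropout, about 80 in total (Section 2.5). 1:1 allocation (Section 2.3.3).

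**Inputs assumed, because the article does not give them.** The pre-post correlation rho within a test (0.5, range 0.4 to 0.6). The common correlation r between the five test statistics (0 to 0.8).

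**Step 1: reproduce the planned size.** For the group-by-time interaction with 2 groups and 2 time points, the noncentrality is lambda = f² × N × 2 / (1 − rho), with 1 and N − 2 degrees of freedom. At rho = 0.5 the smallest even N that reaches 80% is 68:

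- lambda = 0.030625 × 68 × 2 / 0.5 = 8.33
- power at alpha 0.05 = 81.2%
- 68 / 0.85 = 80

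This matches the article. With rho = 0.4 the total would be 95, and with rho = 0.6 it would be 64, so 0.5 is the likely planning value.

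**Step 2: error if any one of five tests counts.** If the tests are independent, 1 − 0.95⁵ = 22.6%. For correlated tests, five equicorrelated normal statistics were simulated (2 million draws), each tested at two-sided 5%:

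| r | Either direction | In favour of PICMOA |
|---|---|---|
| 0 | 22.6% | 11.9% |
| 0.3 | 20.9% | 10.5% |
| 0.5 | 18.3% | 9.2% |
| 0.6 | 16.7% | 8.4% |
| 0.8 | 12.7% | 6.3% |

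The benchmarks for one test are 5% and 2.5%. For the two fluency tests alone, the two-sided figure is 9.8% at r = 0 and 8.7% at r = 0.6.

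**Step 3: per-test power with 68 completers if all five stay primary.** The strictest step of Holm's procedure over five tests uses alpha 0.05 / 5 = 0.01.

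| rho | lambda | Alpha 0.05 | Alpha 0.01 |
|---|---|---|---|
| 0.4 | 6.94 | 74% | 50% |
| 0.5 | 8.33 | 81% | 59% |
| 0.6 | 10.41 | 89% | 72% |

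At rho = 0.5, 80% power per test at alpha 0.01 would need 100 completers, or 100 / 0.85 = 118 randomised. Recruitment closed with 81.

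**The case against.** The strongest objection is that this is a condensed article and that a statistical analysis plan may supply the hierarchy, adjustment or success rule. Section 2.7 does not say that the P-values are unadjusted, and an adjusted P-value is also compared with 0.05. This stands in part: a reader might infer that the sponsor has decided against adjustment, and the article does not show that. What remains is what the article itself fixes: a five-test primary, one threshold for all analyses, and a sample size that rests on a different set of outcomes.

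A reader might also take a family-wise error of 17% to 23% as established. It is not. It requires that any one of five tests suffices, which the article nowhere states. It also stops at a between-test correlation of 0.6 and counts significant harm as well as benefit. If all five tests had to succeed, the error would be below 1% for correlations from 0 to 0.8. Power would then be the difficulty.

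A third tempting inference is that the stated 80% power fails once error is controlled. That is not true in general. The fall from 81% to 59% is for one given test at alpha 0.01 and rests on an assumed pre-post correlation of 0.5. If one success out of five is enough under Bonferroni, and the same correlation holds, power is about 88% to 99% when all five effects equal f = 0.175. It is about 76% to 86% when only the two fluency tests respond (between-test correlation 0.6 to 0). Holm does at least as well.

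Finally, the Discussion concedes that size was limited by feasibility and looks to larger trials for confirmation. That softens the consequence but does not settle what the primary result is.

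**Conclusion.** The point holds in a conditional form. The article makes a five-test domain primary without saying which result or combination decides the trial, and it powers only the fluency pair with one 5% alpha. If one significant test is taken as a positive primary result, the two-sided error is about 13% to 23%, and the error in favour of PICMOA is about 6% to 12% against 2.5%. Under that reading the error is at least doubled across the whole assumed range of correlations. The size depends on the success rule and on the between-test correlation, and the article gives neither. The mismatch between the primary set and the powered set depends on no assumption.

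**What to change.** Before the post-intervention data are analysed, name one primary outcome, tested at two-sided 5%, in the analysis plan and the registry entry. Two choices fit the article:

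- **One verbal fluency test.** Phonemic fluency has the support of the prior trial described in the Introduction and lies within the sample-size basis.
- **A prespecified composite of the five tests.** This keeps the stated construct of cognitive functioning. Its scoring would have to be defined in advance, and the sample-size reasoning restated for it.

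In either case the tests that are not the primary outcome become secondary. Alternatively, keep all five as primary, apply Holm's procedure and restate the power, giving the pre-post correlation used. Section 2.5 should then refer to the same outcome or set of outcomes as Section 2.4.1.

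The change is to wording and needs no further data or participants. With one primary outcome, the demoted tests can no longer support a primary claim. With Holm, per-test power is lower, at about 59% on the strictest step with 68 completers and a pre-post correlation of 0.5, and completed recruitment leaves no room to make that up.
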